### Intervention

Subjects of all three RCTs participate in the same lifestyle program in mixed groups.

The program starts with a personal intake by a dietitian, reviewing general health, dietary habits, and physical activity. With a physical therapist, personal goals for physical activity are set (and reset at the beginning of the extension period). The lifestyle program consists of 10 group meetings (with 6–12 participants) for 2–3 h each (see supplement 2). During the program theoretical education about a WFPD, exercise, and stress is combined with a practical cooking class (with partner or relevant other person, in the first meeting), relaxation exercises and physical training, supported by podcasts, videos, and at-home exercises. The control group receives usual care, is advised not to change usual behavior, and enters the program after 16 weeks.

The WFPD is based on protocols by Ornish and Barnard [28, 45], although recommendations on fat are adapted to Dutch guidelines (20–35/40% of energy instead of low fat [max 10% of energy]). The proposed diet is in line with the 2015 Guidelines on Healthy Nutrition of the Health Council of the Netherlands. Subjects will be facilitated by means of fully elaborated week plans (developed by registered dietitians, in line with recommended daily allowances, see example in Fig. 3), and they will receive supplementation for vitamin B12 and D [46]. To promote weight loss, overweight and obese patients are motivated to limit meal frequency to three meals per day. The program contains a short “green fasting” protocol (see supplement 3) [9–13], as recommended by the *program Ambassadors*. The *program Ambassadors* are fifteen target group patients, who are involved in the development of the lifestyle program and the analyses. These lay experts had experienced improvement in their own health status with diet adaptations, exercise, and/or use of stress management techniques.

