**Fig. 3 Fig3:**
[figure not shown]
Example of a week menu

Recommendations for physical activity and exercise are based on the Dutch physical activity guidelines 2017 and the protocol by Ornish [28, 47]. Group exercise is focused on moderate exercise, fun, and group cohesion. Patients will be motivated to integrate physical activity in daily activities (example: walk/cycle more rather than sitting in a car or public transport) and search for possibilities to exercise in their neighborhood.

Stress management is based on protocols by De Brouwer et al. [48]. Subjects will receive psychoeducation on the effects of stress on health and on stress management, as well as guided practice and home exercises (supported by tools, such as audio/Apps) on relaxation techniques and breathing and visualization exercises, as well as coaching on sleep [48].

A specification of the subjects covered in the 10 group meetings is available in supplement 2.

During the 2-year extension study, 6 facultative meetings will be organized for participants on varying subjects from the three categories (examples: weight loss, how to stay active, self-compassion). After the 16-week intervention, medication of subjects with RA with minimal disease activity (DAS < 2.6) will be tapered by the participants’ rheumatologists, who are supplied with a standardized scheme (see supplement 4). If disease activity increases after tapering, medication will again be increased back to the previous step. For participants in the MSOA group, pain medication will be monitored.

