### Sample size calculation

Based on *α* = 0.05 and power (1-β) = 0.80, effects ranged from 0.4 to 1.0 decreases for the DAS28 (estimated from component data of the DAS28 in the case of the trial by Kjeldsen Kragh et al.) with standard deviations (SD) ranging from 0.6–1.0 [12, 14]. The minimal clinically important improvement (MCII) in the DAS28, however, increases with higher baseline values and vice versa [60]. In the range of our inclusion criterion of DAS28 (between 2.6 and 5.1), the MCII is 0.8. Sköldstam et al. reported a difference in the DAS28 of 0.5 in 12 weeks [14]. In our 16-week study, we expect an additional effect on top of that provided by diet alone, due to the combination with exercise and stress management. Based on clinically relevant effect sizes of delta 0.8 with a SD of 1.2 for the DAS28, *α* of 0.05, and *β* of 0.2, we need a sample size of 56.

For OA patients, we found effects ranging from 2.2 to 2.8 for WOMAC pain (OA) and 5.7 to 10 for WOMAC function (OA) and standard deviations (SD) ranging from 0.4 to 0.6 with an exceptional 3.1 for WOMAC pain and 1.4 to 3.1 with an exceptional 10.9 for WOMAC function [15, 61, 62]. Based on these studies, we estimated that a power of 0.80 is feasible with a total of 60–70 subjects (intervention + control group) and planned to aim for 80 subjects for both RA as well as OA patients (total 160 patients) based on a possible dropout rate of approximately 20%.

For patients with ACPA-positive arthralgia, we added a pilot group of 16 participants (*n* = 8 intervention group, *n* = 8 waiting-list control group).

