### Statistical analysis

At baseline, half-way (8 weeks) and at the end of the study (16 weeks) outcomes are measured (see supplement 5 for a specification of the measurements).

After conclusion of the randomized controlled trial, data will be cleaned, verified by two researchers, and inspected for errors, inconsistencies, and incomplete information. Outliers will be inspected and corrected if necessary.

Primary outcomes DAS28, RA risk-scores, and WOMAC (all continuous variables) at 8 and 16 weeks in the intervention group will be compared with outcomes at 8 and 16 weeks in the control group, adjusted for baseline scores. Intention-to-treat analyses will be performed, with additional per-protocol analyses. For the analyses, a repeated measures mixed model will be used with random effect for the subjects and fixed effects for group (intervention or control) and baseline values for DAS28, RA risk-score, or WOMAC.

Secondary outcome measures (physical function, fatigue, pain interference, depression, waist circumference, fat mass, blood pressure, LDL, HDL, triglycerides, fasting glucose and ESR) will be analyzed the same way as the primary outcomes. Statistical tests will be limited to primary and secondary outcomes. For other outcomes, descriptive statistics will be used. We will analyze microbiome, remaining metabolic and stress-related outcomes separately and report results in dedicated articles.

In the extension study, the primary and secondary outcomes of the intervention study will become secondary outcomes, and adherence will be the primary outcome. These outcomes are analyzed in the same way as the intervention study, using the baseline, halfway, and end measurements from the 16-week intervention program, as well as 6-, 12-, and 18-month and end (24 month) measurements of the extension study. Intention-to-treat analyses will be performed, with additional per-protocol analyses. Since the extension study is observational, a within-subject analysis will be performed using a repeated measures mixed model with random effect for the subjects and fixed effects for baseline values.

*P* values < 0.05 will be considered to be significant.

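### The intervention is given in meeting groups, but the model has no meeting-group term, so standard errors in RCT 1 and RCT 3 may be modestly too small if outcomes correlate within groups

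*Protocol article*

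**What the plan says.** All references are to the Protocol article.

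- **Delivery** (Intervention): "The lifestyle program consists of 10 group meetings (with 6–12 participants) for 2–3 h each". The groups mix patients from the three RCTs. The text on exercise adds: "Group exercise is focused on moderate exercise, fun, and group cohesion".
- **Control arm** (Intervention): usual care for 16 weeks, then entry into the programme. Controls therefore have no meeting group during the randomised comparison.
- **Randomisation** (Recruitment, selection, and randomization of participants): individual patients, 1:1.
- **Analysis** (Statistical analysis): "a repeated measures mixed model will be used with random effect for the subjects". The fixed effects are study arm and the baseline value of the outcome; the word group in that sentence means arm. Secondary outcomes are handled the same way, and "values < 0.05 will be considered to be significant".
- **Sample size** (Sample size calculation): "Based on clinically relevant effect sizes of delta 0.8 with a SD of 1.2 for the DAS28", and from this "we need a sample size of 56". The target is 80 each for RA and OA, allowing for about 20% dropout, plus a pilot of 8 + 8 for RCT 2. No ICC or design effect appears.

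**The concern.** This is a partially nested design. Intervention patients go through ten sessions with the same companions, in a format meant to build cohesion, so their outcomes may be correlated. Control patients have no such link. The planned random effect for subjects deals with repeated visits by one patient. It says nothing about two patients in the same meeting group.

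If the within-group correlation is positive, the model understates the variance of the intervention-arm mean. Confidence intervals are then too narrow and P values too small, so the error runs towards declaring an effect. It would apply to the primary outcome and to every tested secondary outcome in the affected RCTs.

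The article names the random and fixed effects of its model. The point is therefore about a stated choice, not about detail left to an analysis plan.

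**Working it through.** **1. The plan's own figure.** Inputs from Sample size calculation: delta 0.8, SD 1.2, alpha 0.05, power 0.80. Per arm, n = 2(z_alpha + z_beta)² SD²/delta².

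- One-sided alpha: 2 × (1.645 + 0.842)² × 1.44/0.64 = 27.8, so 28 per arm and 56 in total. This matches.
- Two-sided alpha: 2 × (1.960 + 0.842)² × 1.44/0.64 = 35.3, so 36 per arm and 72 in total.

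The stated 56 thus contains no allowance for clustering. It is reproduced only with a one-sided alpha, and the article does not state sidedness. That is a separate matter; the two-sided 5% level is used below.

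**2. Same-RCT patients per meeting group.** Each RCT is analysed separately, so only members of the same RCT form a cluster. The planned intervention arms hold 40 RA + 40 OA + 8 RCT 2 = 88 patients. A group of g members has on average m = g × 40/88 from RCT 1, and the same from RCT 3:

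- g = 6: m = 2.73
- g = 9: m = 4.09
- g = 12: m = 5.45

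Groups of 9 imply about 88/9 = 9.8, or about 10 groups. RCT 2 averages 8/9.8 = 0.8 patients per group.

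**3. Effect on the standard error and the test.** With clustering in one arm only and equal arms, the true variance of the difference divided by the variance assumed under independence is

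R = 1 + (m − 1) × ICC/2.

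The standard error ratio is √R, and the true two-sided type I error of the nominal 5% test is 2[1 − Φ(1.96/√R)]. The ICC is not in the article; 0.01–0.10 is an assumed range.

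| Group size (m) | ICC | R | SE ratio | Type I error |
|---|---|---|---|---|
| 6 (2.73) | 0.01 | 1.009 | 1.004 | 5.1% |
| 6 (2.73) | 0.05 | 1.043 | 1.021 | 5.5% |
| 6 (2.73) | 0.10 | 1.086 | 1.042 | 6.0% |
| 9 (4.09) | 0.01 | 1.015 | 1.008 | 5.2% |
| 9 (4.09) | 0.05 | 1.077 | 1.038 | 5.9% |
| 9 (4.09) | 0.10 | 1.155 | 1.074 | 6.8% |
| 12 (5.45) | 0.01 | 1.022 | 1.011 | 5.3% |
| 12 (5.45) | 0.05 | 1.111 | 1.054 | 6.3% |
| 12 (5.45) | 0.10 | 1.223 | 1.106 | 7.6% |

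A simulation of an unadjusted comparison (40 RA patients per arm, 20,000 trials per setting) agrees: 5.0% at ICC 0, 5.9–6.4% at ICC 0.05 and 5.9–7.8% at ICC 0.10.

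**4. If former controls share the groups.** The article does not say whether waiting-list patients who have crossed over sit in groups with newly randomised patients. If they do, a group of 9 has m = 9 × 40/176 = 2.05. R is then 1.026 (ICC 0.05) or 1.052 (ICC 0.10), and the type I error is about 5.3% or 5.6%.

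**5. Power, for RCT 1.** With 80 less 20%, 32 per arm remain. Under independence the standard error is 1.2 × √(2/32) = 0.30, and two-sided power is Φ(0.8/0.30 − 1.96) = 76.0%. With m = 4.09 the correct standard error is 0.30√R, and power is 72.9% (ICC 0.05) or 69.9% (ICC 0.10).

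**The case against.** The strongest case for the plan has five parts.

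- **No ICC is given.** A reader might infer from the design alone that the intervals are too narrow and the type I error exceeds 5%. The article does not support that as a certainty: at ICC 0 the planned test is correct. If the programme changed nothing for anyone, meeting together would create no correlation in outcomes; inflation needs group effects that vary around a zero mean. This stands, and the point is conditional. Interval coverage does not depend on a zero effect, however: with a positive ICC the intervals are too narrow whatever the mean effect.
- **The clusters are small.** A reader might take all 6–12 members as one cluster and reach 8.0–11.5% at ICC 0.10. That contradicts the mixing of the three RCTs within groups. It also does not hold for every RCT: RCT 2 averages less than one patient per group, so a group term there would be inestimable and is not needed.
- **Leaders.** Nothing says that leaders differ between groups, so no leader effect can be assumed. The argument rests on shared sessions and intended cohesion only.
- **The check is simpler than the planned model.** The formula and simulation have no baseline adjustment and no second follow-up visit. The ICC that matters is the residual one after adjustment, which is unknown. This stands as a limit on precision.
- **About 10 groups estimate a variance component poorly**, and the estimate may be zero. This also stands, and is a reason to accept a sensitivity analysis as the minimum.

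None of this removes the central fact that the stated model has no place for correlation between members of a meeting group.

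**Conclusion.** The point holds in conditional form for RCT 1 and RCT 3. If outcomes correlate within meeting groups, the planned model understates the standard error, and the error favours a positive finding. The size is modest: a type I error of about 5.1–7.6% against a nominal 5%, equivalent to 95% intervals that cover about 92.4–94.9%. For groups of 9 the type I error is 5.9% at ICC 0.05 and 6.8% at ICC 0.10.

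These figures rest on an assumed ICC of 0.01–0.10, full recruitment at 1:1, and average mixing of the RCTs across groups. They shrink if former waiting-list patients share the groups. This does not threaten the trial's validity, but it is a cheap improvement that should be made.

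**What to change.** 1. Record the meeting-group identifier for every intervention patient in the trial database.
2. For RCT 1 and RCT 3, add to the primary and secondary outcome models a random intercept for meeting group in the intervention arm only, with each control as its own unit, keeping the subject random effect. Use Satterthwaite or Kenward-Roger degrees of freedom.
3. If the planned model is kept as primary, prespecify this partially nested model as a sensitivity analysis.
4. Report the estimated ICC for the primary outcomes, and state whether former waiting-list patients shared groups with newly randomised patients.
5. Leave RCT 2 as planned.

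The cost is one model term and one data field. Intervals become slightly wider and some power is lost when the ICC is positive (about 3 to 6 percentage points in the power calculation above). The variance component will be imprecise with about 10 groups. If it is estimated as zero, the model reduces to the planned one.

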**Fig. 3 Fig3:**
[figure not shown]
Example of a week menu

Recommendations for physical activity and exercise are based on the Dutch physical activity guidelines 2017 and the protocol by Ornish [28, 47]. Group exercise is focused on moderate exercise, fun, and group cohesion. Patients will be motivated to integrate physical activity in daily activities (example: walk/cycle more rather than sitting in a car or public transport) and search for possibilities to exercise in their neighborhood.

Stress management is based on protocols by De Brouwer et al. [48]. Subjects will receive psychoeducation on the effects of stress on health and on stress management, as well as guided practice and home exercises (supported by tools, such as audio/Apps) on relaxation techniques and breathing and visualization exercises, as well as coaching on sleep [48].

A specification of the subjects covered in the 10 group meetings is available in supplement 2.

During the 2-year extension study, 6 facultative meetings will be organized for participants on varying subjects from the three categories (examples: weight loss, how to stay active, self-compassion). After the 16-week intervention, medication of subjects with RA with minimal disease activity (DAS < 2.6) will be tapered by the participants’ rheumatologists, who are supplied with a standardized scheme (see supplement 4). If disease activity increases after tapering, medication will again be increased back to the previous step. For participants in the MSOA group, pain medication will be monitored.

### Measurements

#### Primary outcome measures

Main endpoints are the differences between mean changes in the intervention versus control groups from 0 to 16 weeks in:
RCT 1: the DAS28 based on erythrocyte sedimentation rate (ESR), number of swollen joints and tender joints and general health based on the score on a visual analog scale [49] (measured by a blinded research nurse) for RA patients.RCT 2: the RA-risk score (combined score based on RA prevalence in first degree relatives, alcohol consumption, duration, intermittency and location of symptoms, pain, morning stiffness, self-perceived swelling of joints and antibody status) [38] in ACPA-positive arthralgia patients. If a subject develops RA during the study, the RA-risk score will be set to 13 points, the highest possible score.RCT 3: scores on pain, stiffness, and function, combined in the Western Ontario and McMaster Universities Osteoarthritis Index (WOMAC) index [50] for OA patients, measured by the WOMAC questionnaire [51].

Main endpoint for the 2-year extension study for all three groups is the change in adherence from 0 to 24 months, based on an adapted version of the *Lifestyle index adherence score* as developed by Ornish et al [52]:
$$ \left(\mathrm{t}+\left(\left[\mathrm{u}/6+\mathrm{v}/60\right]/2\right)+\left(\left[\mathrm{x}/5+\mathrm{y}/150\right]/2\right)+\mathrm{z}\right)/4 $$

In which *t* = attendance meetings, *u* = stress reduction activities days per week, *v* = stress reduction activities minutes per week, *x* = exercise days per week, *y* = exercise minutes per week, and *z* = adherence to diet.

Adherence to diet (*z*) is defined as ((grams of fiber per 1000 kilocalories/14) + (10/en% SFA))/2 whereby “en% SFA” is defined as the percentage of total kilocalories a day from saturated fatty acids (SFAs). In the original model by Ornish, *z* was defined by total fat and cholesterol intake. Since our protocol is not based on a low-fat WFPD, we changed these vectors into fiber and saturated fatty acids (SFAs) as indicators for a WFPD.

#### Secondary outcome measures

Secondary outcomes are the same for all groups in the three RCTs: RA, ACPA-positive arthralgia, and MSOA, unless otherwise specified. Quality of life-related outcomes measured are self-reported physical, mental and, social health, using the validated Dutch-Flemish Patient Reported Outcomes Measurement Information System (PROMIS®) [53]. In order to select the most important secondary patient reported outcomes, we consulted the *Ambassadors*. From a list of 13 physical, mental and social item banks (see supplement 5), they chose physical function, fatigue, and pain interference as most important. We added depression to this list, since it is strongly associated with the onset of RA [7, 24]. Other secondary outcomes are waist circumference, fat mass (measured by dual-energy X-ray absorptiometry [DEXA]), blood pressure, LDL, HDL, triglycerides, fasting glucose, and ESR.

#### Other outcome measures

Other outcomes related to body composition and metabolism are body weight, height and muscle mass (measured by DEXA). Fifty MSOA patients (30 from the intervention group and 20 from the control group) will be recruited for MRI examination of visceral adipose tissue (VAT), liver fat, and intramuscular fat in the thigh muscle. For the liver and the thigh muscle, the fat content will be determined. In VAT and the thigh muscle, we will characterize the fatty acid distribution based on the peaks in the spectrum representing double and single bonds in the carbon backbone.

Performance-based physical functioning will be measured by grip strength [54] and per get-up-and-go test [55].

Diet (4-7 consequent days digital diary) will be measured using the Dutch ‘Eetmeter’ by ‘Voedingscentrum’ (The Netherlands Nutrition Centre), a validated food diary based on the Dutch food composition database. It is applicable through internet and in the form of an App [56]. Stress is measured using the perceived stress scale (PSS) [57]. In addition, biophysical markers for stress are measured using morning salivary cortisol and heart rate variability (as measured on electrocardiography). Physical activity level will be based on activity data captured by Fitbit Inspire HR wristbands.

We will track metabolic markers such as blood pressure, lipid profile, fasting glucose, and HbA1c and measure pathogenic biomarkers such as RF and ACPA, C-reactive protein, fecal, and oral saliva microbiota 16S composition as well as plasma metabolome changes. Other biomarkers related to dietary intake such as blood markers for folic acid, vitamin B12, calcidiol, hemoglobin, ferritin, leukocytes, thrombocytes, mean corpuscular hemoglobin, creatinine, alanine transaminase, and aspartate transaminase will be measured.

An economic evaluation will be performed to assess the cost-effectiveness of the multidisciplinary lifestyle program compared with usual care for quality-adjusted life-years (QALYs) and the primary outcome measures in all three patient groups. The EQ-5D-5L will be used to measure health-related quality of life. The patients’ EQ-5D-5 L health states will be converted into utility values using the Dutch tariff [58]. QALYs will be estimated by multiplying the patients’ time spent in a certain health state by the respective utility value. Costs will be assessed from a societal (among others informal care, absenteeism costs) and a healthcare perspective [59].

A detailed overview of the measurements is available in supplement 5.

### Sample size calculation

Based on *α* = 0.05 and power (1-β) = 0.80, effects ranged from 0.4 to 1.0 decreases for the DAS28 (estimated from component data of the DAS28 in the case of the trial by Kjeldsen Kragh et al.) with standard deviations (SD) ranging from 0.6–1.0 [12, 14]. The minimal clinically important improvement (MCII) in the DAS28, however, increases with higher baseline values and vice versa [60]. In the range of our inclusion criterion of DAS28 (between 2.6 and 5.1), the MCII is 0.8. Sköldstam et al. reported a difference in the DAS28 of 0.5 in 12 weeks [14]. In our 16-week study, we expect an additional effect on top of that provided by diet alone, due to the combination with exercise and stress management. Based on clinically relevant effect sizes of delta 0.8 with a SD of 1.2 for the DAS28, *α* of 0.05, and *β* of 0.2, we need a sample size of 56.

For OA patients, we found effects ranging from 2.2 to 2.8 for WOMAC pain (OA) and 5.7 to 10 for WOMAC function (OA) and standard deviations (SD) ranging from 0.4 to 0.6 with an exceptional 3.1 for WOMAC pain and 1.4 to 3.1 with an exceptional 10.9 for WOMAC function [15, 61, 62]. Based on these studies, we estimated that a power of 0.80 is feasible with a total of 60–70 subjects (intervention + control group) and planned to aim for 80 subjects for both RA as well as OA patients (total 160 patients) based on a possible dropout rate of approximately 20%.

For patients with ACPA-positive arthralgia, we added a pilot group of 16 participants (*n* = 8 intervention group, *n* = 8 waiting-list control group).

